### Safety assessment

2.8

The patient's vital signs, liver function, and renal function will be recorded at week 4 and week 8. All potential AEs will be accurately recorded at any time. If patients present with any discomfort, or AEs, they are instructed to inform the investigators. The physician will provide necessary treatment to alleviate any AEs.

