**Conclusions::**

The findings of the study will identify the safety and efficacy of Qinghua Zhixie decoction in the treatment of D-IBS.

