### Study design

2.1

The study is a single-center, double blinded, double doomy, randomized, controlled clinical trial. The study has been approved by the Ethics Committee of Changshu Hospital Affiliated to Nanjing University of Chinese Medicine, and the trial will be carried out in accordance with the Declaration of Helsinki. The clinical trial has been registered on open science framework on January 18, 2022 (Registration number: DOI 10.17605/OSF.IO/C8MHW). The protocol conforms to the Standard Protocol Recommendations for Interventional Trials (SPIRIT) 2013 statement,^[20]^ and the results will be reported according to the CONSORT statement extension for trials.^[21]^ The schedule of enrollment, interventions, and assessments is shown in Table 1.

**Table 1 T1:** Schedule of enrollment, intervention, and assessments.

	Enrollment	Treatment					Follow up
Time point	Week 0	Week 1	Week 2	Week 4	Week 6	Week 8	Week 16
Enrollment							
Eligibility screen	√						
Informed consent	√						
Demographics	√						
History of disease	√						
Allocation	√						
Intervention							
QZD+PB-simulation		√	√	√	√	√	
PB+QZD-simulation		√	√	√	√	√	
Assessments							
IBS-SSS		√	√	√	√	√	√
IBS-QOL	√					√	√
HAMD scale	√					√	√
Recurrence rate							√
Adverse effects				√		√	

HAMD = Hamilton depression, IBS-QOL = irritable bowel syndrome-quality of life questionnaire, IBS-SSS = irritable bowel syndrome symptom severity score, PB = pinaverium bromide, QZD = Qinghua Zhixie decoction.

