### Exclusion criteria

2.4

(1)Patients with other gastrointestinal diseases, such as gastrointestinal tumors, anal diseases, intestinal obstruction, perforation, tumors, and anal diseases;(2)Patients with a history of bowel surgery;(3)Women in pregnancy, lactation, and menstruation;(4)Patients taking non-steroidal anti-inflammatory drugs within 1 month that may affect visceral sensitivity;(5)Patients with a history of allergies or allergic to Chinese herbs.

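### No pre-treatment vital signs, liver or renal function are scheduled, so an abnormal on-treatment value cannot be classed as pre-existing or treatment-emergent

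*Protocol article*

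**What the plan says.** Section 2.8 (Safety assessment) fixes the timing of the objective safety measurements: "vital signs, liver function, and renal function will be recorded at week 4 and week 8". Adverse events are handled separately and continuously: "All potential AEs will be accurately recorded at any time". Section 2.7 adds a patient diary covering the frequency and severity of adverse events.

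Table 1 (section 2.1) has one safety row, "Adverse effects", ticked at weeks 4 and 8. It has no row for vital signs or laboratory tests at any week. Its week 0 column lists the eligibility screen, consent, demographics, "History of disease", allocation, IBS-QOL and the Hamilton depression scale.

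The five exclusion criteria in section 2.4 cover other gastrointestinal disease ("Patients with other gastrointestinal diseases, such as gastrointestinal tumors, anal diseases, intestinal obstruction, perforation, tumors, and anal diseases"), bowel surgery, pregnancy, lactation and menstruation, recent use of anti-inflammatory drugs, and allergy. Neither they nor the inclusion criteria in section 2.3 mention liver or renal function. Safety is nonetheless a stated aim. The abstract concludes: "The findings of the study will identify the safety and efficacy of Qinghua Zhixie decoction in the treatment of D-IBS".

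**The concern.** Liver and renal function and vital signs are the only objective safety measurements in the article. A value taken at week 4 or week 8 shows that a result is abnormal then. It does not show whether it was already abnormal before the first dose. Patients aged 18 to 70 may enter with an unrecognised abnormality, because nothing in sections 2.3 or 2.4 screens it out, and a disease history does not supply a laboratory value.

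Two things are therefore lost for these measurements: sorting abnormal values into pre-existing and treatment-emergent, and any analysis of change or shift from baseline. Pre-existing abnormalities also add noise to the comparison between the arms. A missing baseline cannot be recovered once dosing has begun.

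**Working it through.** **Is a baseline supplied anywhere?**

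1. Section 2.8 names weeks 4 and 8. Week 0 is not named.
2. The week 0 column of Table 1 lists no vital signs or laboratory tests. The table has no row for them at all, so it neither confirms the week 4 and week 8 timing nor supplies a baseline.
3. Sections 2.3 and 2.4 contain no hepatic or renal criterion, so eligibility does not imply normal values at entry.
4. Where the article intends a pre-treatment value, it says so. Section 2.7.1 includes week 0 for the IBS-SSS, and section 2.7.2 has the questionnaires completed before and after treatment.

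No part of the article supplies a pre-dose value for these measurements.

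**How many abnormal values would be unclassifiable?** The plan gives no figure on this point to reproduce. The one input from the plan is the number per arm, 464 / 2 = 232 (section 2.10, 1:1 allocation). All rates below are assumptions.

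Let b be the share abnormal before treatment, assumed to persist, and q the share of the remainder who become abnormal on treatment. The abnormal share on treatment is b + (1 − b)q, and the pre-existing fraction of it is b / [b + (1 − b)q].

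| b | q | Pre-existing per arm, 232b | New per arm, 232(1 − b)q | Pre-existing fraction |
|---|---|---|---|---|
| 2% | 1% | 4.6 | 2.3 | 67% |
| 2% | 2% | 4.6 | 4.5 | 51% |
| 2% | 5% | 4.6 | 11.4 | 29% |
| 5% | 1% | 11.6 | 2.2 | 84% |
| 5% | 2% | 11.6 | 4.4 | 72% |
| 5% | 5% | 11.6 | 11.0 | 51% |
| 10% | 1% | 23.2 | 2.1 | 92% |
| 10% | 2% | 23.2 | 4.2 | 85% |
| 10% | 5% | 23.2 | 10.4 | 69% |

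**What happens to the comparison between arms?** Take b = 5% in both arms, q = 2% on QZD and q = 0% on pinaverium bromide (PB).

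- Without a baseline, the abnormal shares are 0.05 + 0.95 × 0.02 = 6.9% and 5.0%, a difference of 1.9 points. The standard error is √[(0.069 × 0.931 + 0.05 × 0.95) / 232] = 2.2 points. About 16 against 12 patients gives a Fisher exact p of 0.56.
- With a baseline, the treatment-emergent shares are about 2% and 0%. The standard error is √(0.02 × 0.98 / 232) = 0.9 points. The expected count on QZD is 4.4, against none on PB. Rounded to 5 against 0, Fisher p is 0.06; rounded to 4 against 0, it is 0.12.

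The difference is almost the same either way. The standard error is about 2.4 times as large without the baseline (2.2 / 0.9).

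**The case against.** The strongest reply is that silence in this article is weak evidence. Table 1 is visibly incomplete: it leaves the IBS-SSS unticked at week 0 although section 2.7.1 measures it then, and it omits the Hamilton anxiety scale required by section 2.7.2. The eligibility screen is not itemised, section 2.8 does not use the word only, and participants are inpatients who may well have admission values. A full protocol could hold a screening panel. This lowers confidence but does not dispose of the point, because section 2.8 does not leave timing open: it states the time points, and week 0 is not among them.

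Four stronger readings are tempting, and the document does not support them.

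- A reader might infer that the safety aim cannot be answered. Adverse events are recorded at any time and the diary adds to them; neither needs a baseline laboratory value. The gap is confined to vital signs and liver and renal function.
- A reader might infer that a difference between arms can be seen only with a baseline. Randomisation balances pre-existing abnormality in expectation, so the comparison at weeks 4 and 8 is unbiased. In the illustration it is noisier, and even with a baseline the assumed signal does not reach p < 0.05.
- A reader might infer that harm would be recognised later. A week 4 abnormality is seen at week 4 with or without a week 0 value; what suffers is its interpretation.
- A reader might cite Table 1 as placing these tests at weeks 4 and 8 only. It has no row for them, so that timing rests on section 2.8.

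**Conclusion.** The point holds in a limited form. On the schedule as stated, abnormal on-treatment vital signs and liver and renal results cannot be separated into pre-existing and treatment-emergent, and change from baseline cannot be computed. Under the assumed ranges, 29–92% of abnormal on-treatment values would be pre-existing. In the single between-arm illustration, the standard error rises from about 0.9 to 2.2 percentage points with no bias. These sizes rest on assumed rates and on pre-existing abnormalities persisting through treatment; the loss of classification itself does not depend on them. Adverse event recording, the primary outcome and the sample size are untouched. It is a worthwhile, inexpensive improvement and does not invalidate the safety assessment.

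**What to change.** In section 2.8, add one set of vital signs, liver function and renal function at week 0, before the first dose. Add a row for these measurements to Table 1, ticked at weeks 0, 4 and 8, separate from the adverse effects row. If recent admission values are to serve as the baseline, say so and state how recent they must be. Report treatment-emergent abnormalities and change from baseline by arm. If a week 0 set is already planned in a fuller document, stating it in both places is enough.

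The cost is one extra set of routine tests per participant, at a visit that already exists and with tests the trial already runs twice. Where admission values qualify, there is little or no added testing.

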### Follow-up

2.9

After 8-week treatment, the patients will be followed-up for another 8 weeks to assess the recurrence rate.

### Sample size

2.10

According to our preliminary experiment, QZD and PB are expected to reduce the IBS-SSS by 115 points and 105 points, respectively. Taking α = 0.05, β = 0.2, SD = 37, 212 cases will be needed in each group. Considering a loss to follow-up of 10%, 464 cases in total will be included.

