### Participants

2.2

Participants will be recruited from inpatients in Changshu Hospital Affiliated to Nanjing University of Chinese Medicine, and they will be randomly assigned to either the treatment group and control group by a 1:1 ratio (Fig. 1).

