### Statistical methods

2.14

Statistics will be analyzed with the SPSS 22.0 (SPSS Inc., Chicago, IL). Statistical testing is 2-sided and *P* < .05 is considered statistically significant. Efficacy outcome parameters will be analyzed on an intent to-treat basis, and the last observation carried forward rule will be applied to manage missing data. The results will be reported in descriptive statistics. According to the homogeneity, group *t* test for normally distributed data or Mann-Whitney *U* test for non-normally distributed data will be used to compare variables between groups.

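### The total of 464 does not follow from the plan's own 212 per group and 10% loss, and 212 itself needs checking against the printed inputs; the effect on power is small

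*Protocol article*

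**What the plan says.** Section 2.10 takes its effect from a preliminary experiment: "QZD and PB are expected to reduce the IBS-SSS by 115 points and 105 points, respectively". It continues: "Taking α = 0.05, β = 0.2, SD = 37, 212 cases will be needed in each group". The next sentence reads: "Considering a loss to follow-up of 10%, 464 cases in total will be included".

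Section 2.14 adds what the calculation needs from the analysis side. "Statistical testing is 2-sided", and groups are compared by a "test for normally distributed data or Mann-Whitney" U test otherwise. Efficacy is analysed by intention to treat, with last observation carried forward (LOCF) for missing values. Section 2.2 fixes the allocation: patients are "randomly assigned to either the treatment group and control group by a 1:1 ratio".

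**The concern.** Every input and both results are printed in 2.10, so the paragraph can be checked without any other document. Two things stand out. The total of 464 is 232 per group, which is less than 212 enlarged for 10% loss by either usual rule. If 10% are lost, fewer patients remain than the preceding sentence says are required. Separately, the printed difference, SD, alpha and beta lead to a slightly larger number than 212.

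Both discrepancies run in the same direction. At stake is whether the power on which the trial's size is justified agrees with the number it will randomise.

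**Working it through.** **Inputs.** Difference 115 − 105 = 10 points, SD 37 (taken as common to both groups), alpha 0.05, power 1 − 0.2 = 0.80 and loss 10% (all 2.10); two-sided t test (2.14); 1:1 allocation (2.2). Stated results: 212 per group, 464 in total (2.10).

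**Step 1: the number before loss.**

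n per group = 2 × (z0.975 + z0.80)² × SD² / difference²
= 2 × (1.960 + 0.8416)² × 37² / 10² = 214.9, rounded up to 215.

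The noncentral t version gives 216. A one-sided alpha of 0.05 gives 170, so sidedness does not explain 212.

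The stated 212 is 1.4% below 215 and 1.9% below 216. It can be reproduced if the SD was rounded for print: with SD 36.7 the normal formula gives 211.4, rounded up to 212. Values that print as 37 (36.5 to 37.5) give about 210 to 221 per group.

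**Step 2: the loss allowance, starting from the plan's own 212.**

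| Rule | Per group | Total |
|---|---|---|
| Divide by 0.9 | 212 / 0.9 = 235.6, so 236 | 472 |
| Multiply by 1.1, rounding the total | – | 424 × 1.1 = 466.4, so 467 |
| Multiply by 1.1, rounding each group | 212 × 1.1 = 233.2, so 234 | 468 |
| Stated | 232 | 464 |

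Neither rule gives 464. Read backwards:
- 464 × 0.9 = 417.6, or 208.8 per group, which is below 212.
- The loss that 464 can absorb before falling under 424 is (464 − 424) / 464 = 8.6%.

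With the printed inputs and division by 0.9, the consistent total would be 478 (215 / 0.9, so 239 per group) or 480 (216 / 0.9 = 240 per group). That is 14 to 16 above 464.

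**Step 3: what this does to power.** Two-sided t test, SD 37, noncentrality = difference / (SD × √(2/n)).

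| Situation | n per group | Difference | Power |
|---|---|---|---|
| Stated requirement | 212 | 10 | 79.3% |
| 10% lost and contributing nothing | 209 | 10 | 78.7% |
| All 464 analysed, no dilution | 232 | 10 | 82.8% |
| All 464 analysed, dropouts carry no difference | 232 | 0.9 × 10 = 9 | 74.4% |

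The last row is an assumption, because the protocol gives no figure for how much of the difference carried-forward values retain. Suppose that 10% drop out and keep a fraction f of the 10 points, with the SD unchanged. The average difference is then 9 + f. Power is 74.4% at f = 0, 78.8% at f = 0.5, about 80% near f = 0.65, and 82.8% at f = 1.

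**The case against.** There are three good arguments on the other side.

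*The 212 may be right.* Pilot inputs are usually rounded for print, and 212 lies inside the range of about 210 to 221 given by SDs that print as 37. This stands. A reader might infer that 212 is an error and should be 215 or 216. The protocol does not establish that; it shows only that the figures as printed do not lead to 212. Rounding of the SD does not rescue 464, because the loss step uses only 212 and 10%.

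*The analysis keeps everyone.* Under 2.14, patients who leave early stay in the efficacy analysis through LOCF, so the test would be run on 464 rather than about 418. Nominal power is then 82.8%, above the target. A reader might infer from the 209 per group that 80% power is not delivered. That holds only if lost patients contribute nothing, which is what a loss allowance implies but not what 2.14 describes. Equally, 82.8% is an upper figure: it needs carried-forward scores to show the full 10-point difference, and the protocol says nothing on that.

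*The gap is trivial.* The shortfall at 209 per group is 80 − 78.7 = 1.3 points, which is comparable to the effect of rounding the SD. This also stands, and it limits the point to a correction of the text.

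**Conclusion.** The loss step is wrong as written. From 212 per group and 10% loss the total is 472 by division, or 467 to 468 by multiplication, so 464 is short by 8 or by 3 to 4 patients. This conclusion needs no assumption beyond the plan's own figures.

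The figure of 212 is unconfirmed rather than wrong: the printed inputs give 215 or 216, and an SD of about 36.7 would account for the difference.

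The consequence is minor. Power lies between 78.7% and 82.8%, depending on whether lost patients are left out or are kept by LOCF without dilution. Complete dilution among the 10% who drop out would bring it to 74.4%. These powers assume a t test, a common SD of 37 that LOCF leaves unchanged, and a true difference of 10 points. The point does not threaten the validity of the trial and gives no reason to enlarge it.

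**What to change.** Keep 464. Check 212 against the preliminary data and either correct it or print the unrounded difference and SD. Then restate 2.10 so that the two sentences agree and the analysis set is named, for example:

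> With the inputs as printed, 215 to 216 patients per group give 80% power. Randomising 464 with 10% loss leaves about 209 per group with complete data (78.7% power, two-sided t test). The intention-to-treat analysis of all 464 with last observation carried forward has up to 82.8% power, and less if the carried-forward values dilute the difference between groups.

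If the unrounded inputs do give 212, the requirement and the power figures in this text should be recomputed from them; the correction of the loss step remains.

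The cost is one paragraph. The total in the abstract stays as it is, and enrolment, design and analysis do not change.

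### The 80% power is not assured for the stated intent-to-treat analysis with LOCF: the sample size treats the 10% lost as removed, and what LOCF does to the difference and SD is not allowed for

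*Protocol article*

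**What the plan says.** Section 2.10 (Sample size) takes its inputs from a pilot: "According to our preliminary experiment", "QZD and PB are expected to reduce the IBS-SSS by 115 points and 105 points, respectively". It continues: "Taking α = 0.05, β = 0.2, SD = 37, 212 cases will be needed in each group". It then adds patients for attrition: "Considering a loss to follow-up of 10%, 464 cases in total will be included". Allocation is 1:1 (section 2.2), so 464 means 232 per arm.

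Section 2.14 (Statistical methods) analyses efficacy by intent-to-treat, and "the last observation carried forward rule will be applied to manage missing data". Tests are two-sided at 0.05: a t test if the data are normal, Mann-Whitney U if not. Section 2.7.1 lists IBS-SSS at weeks 0, 1, 2, 4, 6 and 8. Follow-up for recurrence continues to week 16 (sections 2.7.2 and 2.9).

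**The concern.** The two sections treat the same 10% of patients differently. Inflating for loss makes sense when lost patients drop out of the comparison and about 212 per arm remain. Under LOCF nobody drops out: all 232 per arm are analysed, some of them with an early score standing in for week 8.

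This matters here because the fall expected in both arms (105 to 115 points) is far larger than the difference between them (10 points). A drop-out who carries forward little change lies up to about 110 points, or three SDs, from the completers. A modest share of such patients shrinks the mean difference and adds a large variance component. Section 2.10 allows for neither. If the effect is real but the analysis is less sensitive than stated, a null result is more likely than the stated 20%.

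**Working it through.** **Inputs from the article.** Falls of 115 and 105 (difference 10), SD 37, two-sided alpha 0.05, power 80%, 212 per arm, 10% loss, 464 in total (232 per arm).

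**The plan's own figure.** n per arm = 2 × [37 × (1.960 + 0.842) / 10]² = 214.9, so 215 against 212 stated, which is within 3%. With difference 10 and SD 37, power is about 79% at 212 per arm and 83% at 232 per arm. Inflating 212 by 10% gives 468 (212 × 1.1, rounded up to 234 per arm) or 472 (212 / 0.9, rounded up to 236 per arm), against 464 stated. The sample-size arithmetic is not the problem.

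**Adding LOCF.** Assumptions that the article does not supply: the inputs describe patients with the full 8 weeks, a fraction p leaves before week 8 in each arm, and each drop-out carries forward on average a fraction r of the full change, with SD s. Then:

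- difference D = 10 × (1 − p + p·r)
- variance in an arm with mean fall μ = (1 − p)·37² + p·s² + p(1 − p)·[(1 − r)·μ]², averaged over the two arms
- power is that of the two-sample t test with 232 per arm

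*Example, p = 0.10, r = 0, s = 0.* D = 9. Variance with μ = 115: 0.9 × 1369 + 0.09 × 13225 = 2422. With μ = 105: 0.9 × 1369 + 0.09 × 11025 = 2224. The average is 2323, so SD = 48.2. The standard error is 48.2 × √(2/232) = 4.48, D/SE = 2.01, and power is about 52%. Dilution alone (D = 9, SD kept at 37) gives about 74%, so the wider SD is the larger effect.

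*All 10% lost before week 8.* The two ends of each range are s = r × 37 and s = 37.

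| Fraction carried (r) | D | SD | t-test power |
|---|---|---|---|
| 0 | 9.0 | 48.2-49.6 | 50-52% |
| 0.25 | 9.25 | 43.1-44.5 | 61-64% |
| 0.5 | 9.5 | 39.2-40.5 | 71-74% |
| 0.75 | 9.75 | 37.1-37.9 | 79-81% |
| 1 | 10.0 | 37.0 | 83% |

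*Mann-Whitney.* With r at or near 0 the data are clearly non-normal, and section 2.14 would then select Mann-Whitney. Its simulated power is about 61-65% at r = 0 and about 65-66% at r = 0.25. At r = 0.5 the two tests are close.

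*Half of the loss after week 8 (p = 0.05).* At r = 0, D = 9.5, SD is 43.3-44.1 and t-test power is 64-65%. At r = 0.25 power is 71-73%, and at r = 0.5 it is 77-78%.

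*If 115, 105 and 37 already come from an intent-to-treat/LOCF set* with similar drop-out, no adjustment is due and power at 232 per arm is about 83%.

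**The case against.** The strongest reply is that the article never says its inputs describe completers. It names only a preliminary experiment, and if those data were analysed by intent-to-treat with LOCF, 464 patients give more than the stated 80%. This stands. A reader might infer a completer basis from the inflation itself, since LOCF loses no one and would need none. That is suggestive but not proof: trials commonly inflate for loss and then analyse by intent-to-treat.

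Three further points limit the size:

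- **Zero change for every drop-out is the extreme case.** With visits at weeks 1, 2, 4 and 6, it needs every loss before week 1 or no early response. Patients who leave late, or after improving early, cost little or no power.
- **The 50-52% figure is for a t test.** The plan would probably not use that test on such data, and Mann-Whitney loses less.
- **The 10% is not tied to week 8.** Losses between weeks 8 and 16 do not touch the 8-week comparison.

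All three stand and are shown in the ranges above. None of them reconciles section 2.10 with section 2.14. Preferring a mixed model to LOCF is partly a separate argument about missing data, but the LOCF rule is fixed in the text and is what creates the exposure.

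**Conclusion.** The point holds conditionally. The stated 80% is not assured for the stated analysis, because section 2.10 neither allows for carried-forward scores nor says that its inputs already include them.

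If the inputs describe patients with the full 8 weeks and all the loss comes before week 8, power ranges from about 50% (61-65% by Mann-Whitney) to 83%. It reaches 80% only if drop-outs carry forward roughly 70-80% or more of the full change. If the inputs already reflect LOCF, there is no shortfall.

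Two stronger readings are tempting and not supported. One is that the calculation is arithmetically wrong: it reproduces within 3%. The other is that the trial has only 50-74% power: that needs a completer basis and early to mid-course loss, and the article states neither.

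**What to change.** **Section 2.14.** Make the primary analysis a mixed model for repeated measures on the IBS-SSS visits listed in section 2.7.1 (weeks 0, 1, 2, 4, 6 and 8), with the week-8 contrast as the primary comparison. Keep LOCF as a sensitivity analysis. With 10% loss, 464 × 0.9 / 2 ≈ 209 completers per arm remain. They give about 79% power at difference 10 and SD 37, and patients with partial follow-up add some information.

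**Section 2.10.** State which population and missing-data handling produced 115, 105 and 37. Restate power for the analysis that will be run, under explicit assumptions on how many patients leave before week 8 and when. If LOCF stays primary, show a range such as the one above.

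**Cost.** Wording in two sections and slightly more analysis work. The mixed model rests on a missing-at-random assumption, which the sensitivity analysis should probe, and the stated power may look slightly less favourable. No extra patients or visits are needed.
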